## Abstract

**Background:**

The high surgical risk in redo cardiac surgery is largely attributed to adhesions around the epicardium and the great vessels. BAX602 is an adhesion prevention reagent composed of two synthetic polyethylene glycols. Spraying BAX602 over the epicardium and the great vessels reportedly contributes to adhesion prevention after pediatric cardiac surgery. The present study aims to evaluate the safety and effectiveness of BAX602 spray in patients undergoing extracorporeal ventricular assist device implantation surgery to treat refractory congestive heart failure.

**Methods and Design:**

This investigator-initiated, multicenter, pivotal, two-arm, open-label, randomized trial will include a total of 30 patients. The primary outcome measure is the severity of adhesions, which will be evaluated during re-sternotomy surgery performed 2–12 weeks after the primary extracorporeal ventricular assist device implantation surgery. The adhesion severity will be evaluated at five predefined sites using a four-grade adhesion evaluation score (0 = no adhesion; 1 = filmy and avascular adhesion; 2 = dense/vascular adhesion; 3 = cohesive adhesion). This measure will be summarized in two ways to evaluate the effect of BAX602: (1) the total score of the severity of adhesions at all five sites (ranging from 0 to 15), and (2) the total number of sites with dense/vascular or cohesive adhesions (ranging from 0 to 5).

**Ethics and Dissemination:**

The study findings will be disseminated at regional, national, and international conferences and through peer-reviewed scientific journals.

**Trial Registration:**

The trial was registered in the UMIN Clinical Trials Registry (UMIN-CTR: UMIN000038998) on 6 January 2020**.**

## Background

Redo cardiac surgery by re-entry through the sternum carries a substantial surgical risk that is two times greater than the risk associated with the primary cardiac surgery [1–4]. The high surgical risk in redo cardiac surgery is largely attributed to adhesions around the epicardium and the great vessels, which prolongs the cardiopulmonary bypass time and total operation time and increases blood product use, inducing postoperative complications [4, 5]. In particular, the degree of intrapericardial and mediastinal adhesion influences the clinical outcome of redo surgery in patients with an implanted ventricular assist device (VAD) [6]. This increased degree of adhesion after VAD implantation occurs because adhesion is more severe around prosthetic material than native tissue, and the coagulopathic state associated with the VAD exacerbates bleeding during the adhesiolysis, consequently deteriorating the hemodynamic state. Furthermore, in bridge-to-transplantation surgery, the time spent on adhesiolysis limits the time allowed for organ procurement and preservation.

Tissue adhesion after surgical procedures has been well studied at the cellular and molecular levels [7]. Adhesion is initiated just after the surgical procedures, as macrophages are initially recruited from the circulating blood to the surgically exposed areas. Subsequently, settled and activated macrophages form the basis of adhesion by releasing extracellular matrices within 3 days, and angiogenic activities are launched from this basis. Within 5 days, a new vessel network is integrated between the tissues to form structured adhesion tissue [8]. While the structured adhesion tissues are gradually cemented during the subsequent 2 months, new adhesion tissues are not formed after 7 days postoperatively [7, 9]. It is thus suggested that inhibition of the recruitment, settlement, and activation of macrophages to the surgically exposed area for at least 7 days may substantially contribute to the prevention of adhesion tissue formation.

Several adhesion prevention reagents have been proposed. The application of Coseal spray (Baxter Healthcare Corporations, Deerfield IL, USA), hereafter referred to as BAX602, over the epicardium and the great vessels reportedly contributes to adhesion prevention after surgical procedures, including cardiac surgery [10, 11] and even VAD implantation surgery [12, 13]. BAX602 is composed of two synthetic polyethylene glycols (PEGs): a dilute hydrogen chloride solution and a sodium phosphate/sodium carbonate solution. When these two solutions mix, they polymerize to form a hydrogel that inhibits adhesion formation. Spraying the heart and the great vessels with BAX602 causes this hydrogel to coat the surface of the heart and the great vessels; this hydrogel coating is sustained for 7 days before being hydrolyzed, consequently preventing adhesion formation over the surface of the heart and the great vessels [11]. Although there are positive reports of the use of BAX602 in pediatric cardiac surgery in observational [11] and prospective randomized [10] studies, the safety and efficacy of BAX602 for adhesion prevention have not been fully established in adult patients with an implanted VAD.

Because no devices have been approved in Japan for tissue adhesion prevention of thoracic organs, including cardiac surgical cases, this investigator-initiated trial of BAX602 was designed as a multicenter phase I/II randomized controlled study. The aim of this proposed study is to evaluate the safety and effectiveness of spraying BAX602 over the surface of the heart and great vessels for adhesion prevention in patients undergoing extracorporeal VAD implantation surgery to treat refractory congestive heart failure. The subsequent goal of this study is the approval of BAX602 for adhesion prevention in cardiac surgery in Japan.

## Methods and Analysis

### Study Purpose

The present study aims to evaluate the effects of BAX602 in preventing adhesions around the epicardium and the great vessels in patients undergoing extracorporeal VAD implantation for refractory congestive heart failure.

### Study Setting

The study is an investigator-initiated, multicenter, pivotal, two-arm, open-label, randomized trial. The flowchart of the trial is shown in Fig. 1.

**Fig. 1 Fig1:**
[figure not shown]
Summary of the Study Design. VAD, ventricular assist device

### Assessment of Adhesion

Pericardial adhesion will be macroscopically evaluated during VAD explant surgery performed 2–12 weeks after the primary surgery. The VAD explant surgery is performed to either wean the patient from the VAD as a result of sufficient cardiac functional recovery or to exchange the initial VAD with a durable VAD as a result of insufficient recovery [14]. Patients who undergo VAD explant surgery 1–13 days after the primary thoracotomy will be excluded from the efficacy assessment.

The adhesion severity will be evaluated at the following five predefined sites: (i) anterior surface of the right ventricle, (ii) right lateral surface of the right atrium, (iii) diaphragmatic surface, (iv) left lateral surface of the left ventricle, and (v) surface of the ascending aorta. Adhesion severity will be evaluated using a four-grade scoring system where 0 = no adhesion, 1 = filmy and avascular adhesion, 2 = dense/vascular adhesion, and 3 = cohesive adhesion (Fig. 2) [11].

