**Fig. 2 Fig2:**
[figure not shown]
Evaluation of pericardial adhesion. Pericardial adhesion will be evaluated at the VAD explant surgery performed 2–12 weeks after the primary extracorporeal VAD implantation surgery. The five sites at which the severity of adhesion will be evaluated using a four-grade adhesion evaluation score are: (i) anterior surface of the RV, (ii) right lateral surface of the RA, (iii) diaphragmatic surface, (iv) left lateral surface of the LV, and (v) surface of the ascending Ao. VAD, ventricular assist device; Ao, aorta; PA, pulmonary artery; LA, left atrium; RA, right atrium; LV, left ventricle; RV, right ventricle

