### Study Endpoints

The primary outcome measure is the severity of adhesions at the five predefined sites (Fig. 2). This measure will be summarized in the following two ways: (1) total score of the severity of adhesions across all five sites, ranging from 0 (no adhesions at any of the five sites) to 15 (cohesive adhesions at all five sites); (2) total number of sites with dense/vascular or cohesive adhesions, ranging from 0 (no adhesions or filmy and avascular adhesions at any of the five sites) to 5 (dense/vascular or cohesive adhesions at all five sites). These two summary measures will serve as multiple primary endpoints. As adhesion formation generally begins immediately after surgery, and no new adhesion formation occurs after 1 week postoperatively, the severity of adhesions measured at 2 weeks or more after the primary thoracotomy will be used in the primary analysis of the two primary endpoints [15].

The secondary endpoints are: (1) total score of the severity of adhesions across all five sites at 1–12 weeks after the primary thoracotomy, (2) total number of sites with dense/vascular or cohesive adhesions at 1–12 weeks after the primary thoracotomy, (3) survival at the end of the observation period, (4) re-thoracotomy for hemostasis after primary thoracotomy, (5) transfusion volume during re-thoracotomy, and (6) absence of mediastinitis requiring surgical intervention.

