### Sample Size

The sample size was calculated based on the total adhesion severity score, assuming a mean difference in total score of 5.0 between the two groups and a standard deviation of 3.5, referring to published data [11]. Thus, 12 patients are required in each group, assuming a two-sided t-test with *α* = 0.05 with a power of 80%, and a simple Bonferroni correction to control the type I error rate due to the existence of two primary endpoints (a total alpha of 0.05 was equally allocated to each endpoint, i.e., *α* = 0.025). Based on the simulation, in most scenarios that were considered, a sample size of 12 in each group provided at least 80% power to detect a frequency difference in the total number of sites with dense/vascular or cohesive adhesions across all five sites, using the two-sided Fisher’s exact test at α = 0.025. To allow for a drop-out rate of 30% for the primary analysis of the primary endpoints, 15 patients will be recruited per group, i.e., 30 patients in total.

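### The day 1–13 exclusion and the 2–12 week scoring window conflict with secondary endpoints 1 and 2, which count adhesions from week 1

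*Protocol article*

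**What the plan says.** The protocol article gives these rules on when adhesion is scored and whose scores count.

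- Assessment of Adhesion, opening sentence: "Pericardial adhesion will be macroscopically evaluated during VAD explant surgery performed 2–12 weeks after the primary surgery".
- Fig. 2 legend, the same window: "Pericardial adhesion will be evaluated at the VAD explant surgery performed 2–12 weeks after the primary extracorporeal VAD implantation surgery".
- Assessment of Adhesion, exclusion: "Patients who undergo VAD explant surgery 1–13 days after the primary thoracotomy will be excluded from the efficacy assessment". The sentence does not name the analyses it covers.
- Study Endpoints, primary endpoints: adhesion severity "measured at 2 weeks or more after the primary thoracotomy will be used in the primary analysis of the two primary endpoints". This rule is expressly confined to the primary analysis. It has a lower limit and no upper one, although the Abstract and Assessment of Adhesion both give 12 weeks.
- Study Endpoints, secondary endpoint 1: "total score of the severity of adhesions across all five sites at 1–12 weeks after the primary thoracotomy".
- Study Endpoints, secondary endpoint 2: "total number of sites with dense/vascular or cohesive adhesions at 1–12 weeks after the primary thoracotomy".

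No section exempts secondary endpoints 1 and 2 from the exclusion, and none says that adhesion is scored at an explant before two weeks.

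**The concern.** Secondary endpoints 1 and 2 use the same two summaries as the primary endpoints: the 0–15 total score and the 0–5 count of sites with the two worst grades. What separates them is the window. If patients explanted before day 14 are removed from efficacy altogether, the added week holds nobody, and two of the six secondary endpoints carry almost no information beyond the primary ones.

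The conflict also reaches data collection. The operator makes the score at the re-thoracotomy (Group Allocation). A site that follows Assessment of Adhesion and the Fig. 2 legend could reasonably leave the score blank at a day 10 explant. An analysis plan written later can redefine an analysis set, but it cannot reliably restore an observation that nobody made.

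The timing of explant is a post-randomisation event, driven by recovery or lack of recovery, in an open-label trial. The 1–12 week endpoints are the only stated adhesion analyses that would include patients explanted in the second week, so it matters whether they do.

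**Working it through.** **1. The plan's own figure.** Sample Size states that "12 patients are required in each group, assuming a two-sided t-test with *α* = 0.05 with a power of 80" per cent, with alpha then split to 0.025 per endpoint, "assuming a mean difference in total score of 5.0 between the two groups and a standard deviation of 3.5".

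- Normal approximation: n per group = 2 × (z₀.₉₈₇₅ + z₀.₈₀)² × (SD/difference)² = 2 × (2.241 + 0.842)² × (3.5/5.0)² = 2 × 9.505 × 0.49 = 9.31, rounded up to 10.
- Noncentral t at two-sided alpha 0.025: 11 per group gives power 0.815, and 12 per group gives 0.854.

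The stated 12 per group therefore reaches 80% power. No assessment window enters the formula, so neither the conflict nor its repair changes this figure.

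**2. The windows in days.** Assumed convention: week 1 = day 7, week 2 = day 14, week 12 = day 84.

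| Rule | Days | Length |
|---|---|---|
| Secondary endpoints 1 and 2 (1–12 weeks) | 7–84 | 84 − 7 + 1 = 78 |
| Exclusion | 1–13 | 13 |
| Scoring window (2–12 weeks) | 14–84 | 84 − 14 + 1 = 71 |

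- Secondary window overlapping the exclusion: days 7, 8, 9, 10, 11, 12 and 13, that is 7 days.
- Secondary window after the exclusion: days 14–84, that is 78 − 7 = 71 days, identical to the scoring window.
- If one week is read as day 8, the overlap is days 8–13 and the remainder is still days 14–84.

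The exclusion thus removes the whole of what the secondary window adds, and nothing else from it.

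**3. What difference is left.** Study Endpoints sets no upper limit on the primary window. An explant after week 12 could therefore count in the primary analysis and not in secondary endpoints 1 and 2. That would be the only remaining difference between them, and it disappears if the 12-week limit in the Abstract and Assessment of Adhesion applies.

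**4. Whether the score would exist.** Even if the exclusion is set aside, the opening sentence of Assessment of Adhesion and the Fig. 2 legend still schedule scoring at 2–12 weeks only. Amending the exclusion sentence alone leaves this second conflict in place.

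**5. Size.** The article gives no expected number of explants on days 7–13. Each such patient is 1/15 = 6.7% of an arm. For scale only, the margin between 15 recruited and 12 needed is 3 per arm, or 3/15 = 20%, and that margin has to cover losses of every kind. The number affected could be zero.

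**The case against.** The strongest reply is that the intent is clear. Study Endpoints confines the two-week rule to the primary analysis, and Sample Size ties its drop-out allowance to that same analysis. Specific endpoint definitions would ordinarily prevail over a general sentence elsewhere. The article condenses a full protocol, and analysis sets are normally settled in the statistical analysis plan. On this view one qualifying word has slipped out.

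Much of this stands. The intent is probably as described, and that supports the repair proposed here. It does not make the text consistent. This is not detail left for later: two stated rules disagree, and one of them governs what is recorded in theatre. Video of the surgical field is to be collected at re-thoracotomy and might allow later scoring, but no section plans it.

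Three stronger readings are tempting, and the document does not support them.

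- A reader might infer that early explants would also be dropped from survival, re-thoracotomy for hemostasis and mediastinitis. The exclusion sits under Assessment of Adhesion and follows text on adhesion scoring, Statistical Methods states intention-to-treat, and Table 2 schedules survival with no condition on the explant day. Nothing says that these outcomes lose patients.
- A reader might take secondary endpoints 1 and 2 to be a planned sensitivity check on the exclusion. They could serve as one, but the article gives no rationale for them.
- A reader might apply the 30% drop-out rate to 15 patients and count 4–5 per arm as affected. That rate is an allowance for the primary analysis, not a forecast of second-week explants, and 15 recruited against 12 needed leaves room for only 3.

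**Conclusion.** The point holds as a conflict between current statements. Assessment of Adhesion and the Fig. 2 legend on one side, and the definitions of secondary endpoints 1 and 2 on the other, cannot all be followed. If the exclusion and the scoring window are applied literally, the day 7–13 part of those endpoints is empty and may not be scored, and the endpoints essentially duplicate the primary 2–12 week analysis apart from any explant after week 12.

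The reach is limited to two secondary endpoints. The primary comparison, its alpha and the sample size do not move. The conclusion does not depend on whether one week is day 7 or day 8. How many patients it affects cannot be derived from the document. It merits correction because the repair is nearly free and a score not taken at surgery may be lost.

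**What to change.** Reconcile Assessment of Adhesion, the Fig. 2 legend and Study Endpoints with three edits:

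1. Limit the day 1–13 exclusion to the primary analysis of both primary endpoints.
2. In the opening sentence of Assessment of Adhesion and in the Fig. 2 legend, state that adhesion is scored at every explant from week 1, and that scores from two weeks onward feed the primary analysis.
3. State that scores from explants between week 1 and week 2 enter secondary endpoints 1 and 2.

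The cost is a few sentences, plus a check that the case report form and site instructions ask for the five-site score from week 1. Only scoring and analysis sets change. The timing of surgery, the number of patients and the primary test stay as they are.

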**Fig. 2 Fig2:**
[figure not shown]
Evaluation of pericardial adhesion. Pericardial adhesion will be evaluated at the VAD explant surgery performed 2–12 weeks after the primary extracorporeal VAD implantation surgery. The five sites at which the severity of adhesion will be evaluated using a four-grade adhesion evaluation score are: (i) anterior surface of the RV, (ii) right lateral surface of the RA, (iii) diaphragmatic surface, (iv) left lateral surface of the LV, and (v) surface of the ascending Ao. VAD, ventricular assist device; Ao, aorta; PA, pulmonary artery; LA, left atrium; RA, right atrium; LV, left ventricle; RV, right ventricle

### Study Endpoints

The primary outcome measure is the severity of adhesions at the five predefined sites (Fig. 2). This measure will be summarized in the following two ways: (1) total score of the severity of adhesions across all five sites, ranging from 0 (no adhesions at any of the five sites) to 15 (cohesive adhesions at all five sites); (2) total number of sites with dense/vascular or cohesive adhesions, ranging from 0 (no adhesions or filmy and avascular adhesions at any of the five sites) to 5 (dense/vascular or cohesive adhesions at all five sites). These two summary measures will serve as multiple primary endpoints. As adhesion formation generally begins immediately after surgery, and no new adhesion formation occurs after 1 week postoperatively, the severity of adhesions measured at 2 weeks or more after the primary thoracotomy will be used in the primary analysis of the two primary endpoints [15].

The secondary endpoints are: (1) total score of the severity of adhesions across all five sites at 1–12 weeks after the primary thoracotomy, (2) total number of sites with dense/vascular or cohesive adhesions at 1–12 weeks after the primary thoracotomy, (3) survival at the end of the observation period, (4) re-thoracotomy for hemostasis after primary thoracotomy, (5) transfusion volume during re-thoracotomy, and (6) absence of mediastinitis requiring surgical intervention.

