### Follow-Up

All patients will be followed up to detect any adverse events for 4 weeks after the primary surgery or until re-thoracotomy, whichever is longer. Follow-up will end at 12 weeks after the primary surgery of the last patient (last patient-out). The study schedule is shown in Table 2. The second surgery, in which the degree of pericardial adhesion will be assessed, will be performed via the re-median sternotomy approach.

**Table 2 Tab2:** Schedule of evaluation during the study

	Screening	Primary thoracotomy		4 weeks after the thoracotomy	Re-thoracotomy
		before	after		
Inclusion/exclusion criteria	X				
Signed consent form	X				
Medical/treatment history	X				
Vital signs		X			
Cardiac echography	X				X
Chest Xray	X				X
Laboratory tests	X			X	X
Surgical procedure of the primary thoracotomy			X	X	
Surgical procedure of the re-thoracotomy					X
Medication			X	X	X
Adverse events					
Survival				X	X

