### Statistical Methods

Analysis will be based on the intention-to-treat principle. Continuous data will be presented as mean ± standard deviation or median and range. Categorical data will be presented as frequencies with proportions (%). Group A will be compared with group B for all primary and secondary analyses. For intergroup comparisons, Fisher’ exact test will be used for categorical variables, while Welch’s t-test or Wilcoxon’s rank sum test will be used for continuous variables. In addition, the differences between means or proportions for continuous or categorical variables will be calculated with corresponding 95% confidence intervals, where appropriate.

The two primary endpoints will be analyzed by the Bonferroni–Holm procedure, with equal *α* allocation to control the type I error rate; both endpoints will first be tested at α = 0.025. If one of the endpoints significantly differs between groups but the other does not, the other endpoint will be tested again at the α = 0.05 level.

For the secondary endpoints, categorical variables will be assessed with the chi-square test or Fisher’s exact test, while continuous variables will be assessed with the t-test or Wilcoxon’s rank-sum test, as appropriate. For time-to-event variables, the event-free survival curve will be estimated using the Kaplan–Meier method and will be compared between the two groups using the log-rank test. The hazard ratio with its 95% confidence interval will be calculated using a proportional hazards model.

The analyses will be conducted using the most recent version of SAS (Cary, NC, USA). All tests will be two-sided. The statistical analysis plan, which includes a more technical and detailed elaboration of the principal features stated in the present protocol, will be prepared separately and finalized before the database is locked.

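### The survival endpoint has no common time point, and the stated schedule has no survival check after a re-thoracotomy at week 4 or later

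*Protocol article*

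**What the plan says.** Study Endpoints lists "survival at the end of the observation period" as the third of six secondary endpoints, without a time point.

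The Follow-Up section gives two end points. For each patient: "All patients will be followed up to detect any adverse events for 4 weeks after the primary surgery or until re-thoracotomy, whichever is longer". For the trial: "Follow-up will end at 12 weeks after the primary surgery of the last patient".

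Table 2 marks survival in two columns, 4 weeks after the thoracotomy and re-thoracotomy. It has no later column.

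Assessment of Adhesion fixes when and why the second operation happens: "Pericardial adhesion will be macroscopically evaluated during VAD explant surgery performed 2–12 weeks after the primary surgery". It is done "to either wean the patient from the VAD as a result of sufficient cardiac functional recovery", or, where recovery is insufficient, to change to a durable device.

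For time-to-event variables, Statistical Methods says that "the event-free survival curve will be estimated using the Kaplan–Meier method", with a log-rank test and a proportional hazards model. It does not say which endpoints these are, or how they are censored.

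**The concern.** A proportion alive can be interpreted when every patient's status is read at the same time after randomisation or surgery. Here the reading time appears to be set by the second operation, whose date depends on whether the heart recovers.

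The reading may also come just before the period of most interest. The Background attributes much of the danger of redo surgery to adhesions, and the Discussion describes re-entry cardiac surgery as high-risk. If a barrier against adhesions helps or harms survival, the days and weeks after the redo operation are a natural place to look. A patient who reaches that operation after week 4 is necessarily alive on arrival. If observation stops there, a post-operative death is missing from both the survival endpoint and the adverse event record. Safety is a stated aim and the trial is meant to support approval in Japan, so the gap matters even for a secondary endpoint.

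**Working it through.** The plan states no figure for survival, so there is none to reproduce. The check is what the stated schedule would observe.

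**Inputs**
- Time zero: primary surgery.
- R: week of re-thoracotomy, 2 to 12 (Assessment of Adhesion).
- Per-patient end of follow-up: the later of week 4 and R (Follow-Up, worded for adverse events).
- Scheduled survival checks: week 4 and re-thoracotomy (Table 2).

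**Reading 1: the observation period is the per-patient rule**

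End of observation = max(4, R) weeks. Time observed after the redo operation = max(4, R) − R = max(0, 4 − R) weeks.

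| R (weeks) | Observation ends (week) | Days observed after redo |
|---|---|---|
| 2 | 4 | (4 − 2) × 7 = 14 |
| 3 | 4 | (4 − 3) × 7 = 7 |
| 4 | 4 | 0 |
| 8 | 8 | 0 |
| 12 | 12 | 0 |

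Survival is therefore read between week 4 and week 12, a threefold spread (12 / 4 = 3). For R of 4 weeks or more, the scheduled post-operative observation is zero whatever the distribution of R.

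The share of patients affected depends on explant timing, which the article does not give. It is 0% if every explant falls before week 4 and 100% if every explant falls at week 4 or later. Purely as an illustration, with R spread evenly over weeks 2 to 12, the share is (12 − 4) / (12 − 2) = 80%. The mean observation after the redo operation is then 20% × 7 days = 1.4 days, because the other 20% average one week.

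**Reading 2: the observation period runs to trial close**

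The last patient has 12 weeks. A patient operated on d weeks before the last has 12 + d weeks. Enrolment runs from January 2020 to May 2021, so d differs between patients and no common horizon results. Post-redo deaths would count in principle, but Table 2 contains no survival check after re-thoracotomy from which to learn of them.

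**Comparison**

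Neither reading gives one time point for all patients. Reading 1 also omits the period after most redo operations unless explants cluster before week 4. Table 2's survival row matches Reading 1 and has no counterpart for Reading 2.

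**Does a 12-week check fit the trial?**

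May 2021 plus 12 weeks is August 2021, the stated completion date, and follow-up already runs until the last patient reaches 12 weeks. The trial is not lengthened.

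**The case against.** The strongest reply is that the link between the survival endpoint and the re-thoracotomy rule is inferred. The rule is worded for adverse events, the observation period is undefined in this article, and the next sentence gives a different, trial-level end. The definition may stand in the full protocol or the analysis plan. This is fair, and the article cannot be said to state that survival follow-up stops at re-thoracotomy. But Table 2 schedules survival at exactly the two points in the rule, and the alternative reading also lacks a common time point. An analysis plan can define a period or a censoring rule. It cannot supply visits that the schedule leaves out.

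Table 2 also should not be read too literally. Its adverse event row is blank in the text as extracted, and the re-thoracotomy column has no stated duration, so some peri-operative observation may be intended. The supportable statement is that nothing is scheduled after a redo operation at week 4 or later, not that nothing would ever be recorded.

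Two stronger readings are tempting and are not supported:

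- A reader might infer that individual observation stretches to about 19 months, counting from January 2020 to August 2021 for a patient never explanted. That applies the re-thoracotomy rule to explanted patients and trial close to the rest, a combination that no section states. The Discussion also expects explant within 2–3 months.
- A reader might infer that the log-rank test and hazard ratio are biased by informative censoring at explant. Statistical Methods states no censoring rule and does not name survival among the time-to-event variables. Explant is tied to cardiac recovery or its absence, and nothing in the article shows that its timing would differ between arms. Unequal follow-up within both randomised arms is not in itself a between-arm bias.

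Finally, survival is one of six secondary endpoints in 30 patients, and the sample size rests on adhesion. That limits the weight of the point without removing it.

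**Conclusion.** The point holds in a limited form. As written, secondary endpoint 3 is not read at a common time under either available meaning of the observation period. On the reading that Table 2 supports, the end falls between week 4 and about week 12 according to clinical course. Scheduled observation after the redo operation falls from 14 days (operation at week 2) to none (week 4 or later), so deaths after that operation can go uncounted.

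This rests on one assumption: that the adverse event follow-up rule also governs survival. If the period means trial close instead, the loss of post-redo deaths is no longer built into the definition, but unequal follow-up and the lack of a supporting visit remain. The 80% figure is an illustration under evenly spread explant times, not an estimate for this trial. No direction or size of between-arm bias is claimed. The analysis of the primary endpoints is unaffected. The change is worth making because it is cheap and the missing data cannot be restored at the analysis stage.

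**What to change.** - In Study Endpoints, define survival as vital status at 12 weeks after primary surgery for every randomised patient, whether or not re-thoracotomy has occurred.
- In Table 2, add a 12-week status check for survival and serious adverse events, and align the Follow-Up wording with it.
- In Statistical Methods, state that any time-to-event analysis of survival is not censored at explant.

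The cost is one status check per patient, at most 30, within the existing trial duration. The limitation is that a patient explanted near week 12 still has little post-operative follow-up. The common horizon makes the arms comparable at one time point but does not guarantee a minimum period after the redo operation. If the sponsor wants that guarantee, a fixed interval after re-thoracotomy would be needed in addition.
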